#### Adverse events

Perioperative adverse events, which include bradycardia, laryngeal spasm or bronchospasm, allergic reaction, arrhythmia, cardiac events (myocardial infarction, vasospasm, or cardiac arrest), or massive bleeding, will be monitored by the research team and all serious adverse events will be reported to the institutional review board (IRB). The duration and severity of intraoperative hypotension will be assessed using an area under a mean arterial pressure threshold which is defined as the depth below the threshold multiplied by duration, expressed as mmHg * Time (Liem et al. 2020). Awareness with recall will be assessed using the Modified Brice Questionnaire at least 6 h after the end of surgery when the patients are fully alert (Brice et al. 1970). The patient who develops delirium will be assessed following delirium resolution. Undesirable patient movement during surgery will be recorded and graded following criteria. Mild: undesired spontaneous breathing or non-purposeful movement with no impact on the surgery or patient outcome. Moderate: movement that mildly impacted the surgery (e.g., required a pause in the surgery for coughing or straining) and required deepening of anesthesia, deepening of analgesia, or increased muscle relaxant. Severe: movement with a marked negative impact on the surgery (e.g., a patient injury, loss of sterility of the surgical field, purposeful movements suggestive of awareness, or other surgical complication (Wildes et al. 2019).

Postoperative neurologic and non-neurologic complications will be assessed using the example of complication grades proposed to define and grade neurosurgical postoperative complications based on the Clavien-Dindo classification (Landriel Ibañez et al. 2011).

### Perioperative non-endpoint data collection

Patient’s baseline and perioperative data will be collected by investigators who are unaware of the group allocation. Data will be entered into predetermined CRF and a final analysis will be conducted when all the participants finish 3-month follow-up.

#### Preoperative data collection

Sensory impairment (Morandi et al. 2021), alcoholism, history of depression, history of falls within 6 months, history of obstructive sleep apnea, level of education, functional status determined by the Barthel Activities of Daily Living index score (Mahoney and Barthel 1965), frailty score (Abellan van Kan et al. 2008), Charlson’s comorbidity index (Quan et al. 2011), type of surgery, neurologic deficit, polypharmacy (Hein et al. 2014), use of cholinergic antagonists, dopamine agent, lithium, benzodiazepine drug, fluoroquinolone, corticosteroid, or opioid analgesics and preoperative laboratory results, including electrolytes and blood counts will be recorded.

#### Intraoperative data collection

Intraoperative measures, including operative and anesthesia time, anesthetic concentration, perioperative use and dosage of sedatives and opioids, electroencephalographic (EEG) data, hemodynamic data, use of inotropic or vasopressor agents, use of a chronotropic agent for the treatment of bradycardia, total infused volume of crystalloid, transfusion, estimated blood loss, and urine output, will be obtained from patients’ electronic medical records.

#### Postoperative data collection

Pain severity (least and worst) was assessed by NRS from the postoperative day 0 to 5, with 0 (no pain) to 10 (extreme pain). The daily cumulative opioid requirement will be determined from the medical record and quantified using parenteral morphine equivalent (mg) (Ballantyne et al. 2018) until the final delirium assessment is complete. Sleep quality, which is evaluated with the NRS (an 11-point scale where 0 = the worst sleep, and 10 = the best sleep) once daily between 8 and 10 AM) within the 5 days after surgery. The number of valid delirium assessments, along with the reasons why 3D-CAM or CAM-ICU assessments are not conducted, will also be collected.

### Prespecified additional analyses and substudies

#### A. Comparing the incidence and severity of postoperative nausea and vomiting between the remimazolam-based TIVA and propofol-based TIVA

Neurosurgical patients are at high risk for the PONV (ref). Propofol-based TIVA in patients undergoing craniotomies has been associated with a lower incidence of PONV compared to inhalational anesthesia (Chui et al. 2014). Furthermore, a recent meta-analysis demonstrated that perioperative benzodiazepine administration reduced the risk of PONV (Au et al. 2024). In this regard, neurosurgical patients with multiple PONV risk factors are likely to benefit from remimazolam as the primary general anesthetic agent.

#### B. Intraoperative EEG and POD

In the study, EEG data from the BIS monitoring device will be collected in both groups. The intraoperative EEG profile of patients who do and do not develop POD will be compared, and the association with intraoperative EEG and POD will be evaluated.

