## Background

Neurovascular surgery needs neuronal evoked potential monitoring to provide real-time feedback for possible nerve damage. Waveforms acquired during evoke potential monitoring, especially motor and sensory evoked potential monitoring, can be adversely affected by inhalational anesthetics (Schindler et al. 1998). Therefore, total intravenous anesthesia (TIVA) using propofol was identified as the preferred method of maintenance during neurosurgery which needs neuromonitoring (Walker et al. 2020).

Remimazolam, a new short-acting benzodiazepine, has recently gained approval as an intravenous anesthetic for the induction and maintenance of general anesthesia. It has high water solubility and is hydrolyzed by tissue esterase into an inactive metabolite, which allows a rapid onset of sedation/anesthesia and prompts arousal despite prolonged use. In addition, it could be rapidly reversible by an antidote of benzodiazepine, flumazenil (Kim 2022). In the American Society of Anesthesiologists (ASA) physical status class I and II patients undergoing general anesthesia, the remimazolam-based TIVA has shown comparable efficacy as a general anesthetic to propofol-based TIVA while demonstrating a superior safety profile (Doi et al. 2020). Remimazolam has exhibited a lower incidence of hypotension, reduced vasopressor requirements, and fewer instances of bradycardia compared to propofol-based TIVA (Doi et al. 2020). Remimazolam would be quite appealing in patients undergoing cerebrovascular surgery because early emergence from anesthesia is critically important for early neurological assessment and maintaining perfusion pressure is essential to prevent cerebral ischemia in this population (Teixeira et al. 2024).

Despite these promising properties of remimazolam as a general anesthetic, however, there is currently limited evidence about the relationship between remimazolam and postoperative delirium (POD). It may mitigate POD risk by averting intraoperative hypotension, yet as a benzodiazepine, it could potentially increase the risk (Inouye et al. 2014; Kappen et al. 2022; Vasilevskis et al. 2012; Wachtendorf et al. 2022).

POD is associated with increased morbidity, mortality, and healthcare costs (Inouye et al. 2014). The 1-year survival probability is reduced by approximately 10% for each additional day of POD (Pisani et al. 2009). Additionally, it is closely related to long-lasting postoperative cognitive dysfunction (Goldberg et al. 2020).

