### Randomization and blinding

Patients will be randomly allocated to either the propofol or remimazolam group in a 1:1 ratio. Block randomization with random permuted block sizes of 4, 6, and 8 was used to ensure a similar number of subjects in each arm over time while minimizing predictability. A randomization code will be generated on the website (sealedenvelope.com) by an independent research assistant who will not be involved in patient care, pack the allocation group in sequentially numbered, opaque envelopes with identical shapes and sizes, and then give the envelope to attending anesthesiologist and nurse. The investigators who will enroll study participants will be blinded to the group allocation.

The group allocation will be blinded to the people as follows: (1) patients: patients are under general anesthesia during the intervention, (2) surgeons: the anesthesia process is initiated prior to the surgeon’s entry into the operating room. This is followed by the placement of opaque drapes that effectively prevent the surgeon from observing any details of the anesthesia technique. The opaque drapes remain in place from the induction of anesthesia throughout the entirety of the surgical procedure, (3) attending anesthesiologists: Anesthesiologists in the operating room cannot be blinded to randomization assignment but are not involved in the study enrollment or assessment of the results, (4) the outcome assessor will be blinded to the group allocation and evaluate the postoperative outcomes. Group allocation is only opened when all the collected data are ready for statistical analysis.

In a medical emergency, such as deterioration of the patient’s condition intraoperatively or adverse events postoperatively, the blindness will be unmasked by the request from the attending anesthesiologist to the principal investigator.

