### Anesthetic care

Patients will not receive any premedication (usually including anticholinergics and sedatives). On arrival at the operating room, the patient will be applied standard monitoring including pulse oximetry, non-invasive arterial blood pressure, and electrocardiography. Anesthesia will be induced and maintained with study drugs with respect to the group allocation, propofol or remimazolam. To facilitate endotracheal intubation, 0.6–1 mg/kg of rocuronium will be administered and mechanical ventilation will be carried out with a tidal volume of 8 mL/kg, inspiratory: expiratory ratio of 1:2, a fraction of inspired oxygen of 0.5 supplemented with air, and positive expiratory pressure of 5 cmH_2_O. The respiratory rate will be modified to maintain normocarbia. The anesthetic depth will be monitored using a BIS monitor (BIS™; Medtronic, Dublin, Ireland) and maintained between 40 and 60. Continuous invasive blood pressure monitoring using an arterial catheter will be performed. Blood pressure and heart rate will be maintained within 20% of baseline during the surgery. Attending anesthesiologists will be discouraged from administering anticholinergics and intravenous hypnotic agents (e.g., midazolam, ketamine, dexmedetomidine, etomidate) except for their study drugs during the maintenance period. In case of bradycardia, glycopyrrolate or atropine will be administered, and their dose will be recorded. At the end of the surgery, 5-hydroxytryptamine 3 receptor antagonists will be administered as prophylaxis for postoperative nausea and vomiting, and 0.01 mg/kg hydromorphone will be administered for pain control. Sugammadex will be administered for the reversal of neuromuscular blockade. After confirming the reversal of neuromuscular blockade and the patient’s obeying, the patients will be extubated and transferred to the ICU. If the patients cannot obey or in case of surgeon’s request, they will be transferred to the ICU with intubated state.

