## Discussion

In this trial, we aimed to assess the non-inferiority of remimazolam, a new short-acting benzodiazepine, in terms of POD occurrence compared to the conventional intravenous anesthetics, propofol.

Remimazolam demonstrates a favorable pharmacokinetic and pharmacodynamic profile for general anesthesia. However, using benzodiazepines as the principal general anesthetic raises concerns among clinicians about the potential risk of increasing the incidence of POD. Sedation with benzodiazepines in the ICU has been associated with a higher incidence of delirium compared to non-benzodiazepines (dexmedetomidine, propofol) (Casault et al. 2021; Pandharipande et al. 2006; Zaal et al. 2015). Nevertheless, this evidence primarily stems from observational studies. Moreover, long-acting benzodiazepine drugs are more likely to increase the risk of POD compared to short-acting ones. Observational cohort studies have demonstrated no significant increase in the incidence of POD incidence with remimazolam as a general anesthetic in high-risk elderly populations compared to control groups (Aoki et al. 2023; Kaneko et al. 2023). In addition, a recent prospective randomized controlled trial involving 320 patients aged over 60 undergoing elective orthopedic surgery demonstrated a statistically insignificant difference in POD between remimazolam (15.6%) and propofol anesthesia (12.4%) (Yang et al. 2023). Meanwhile, patients in the remimazolam group experienced a lower incidence of post-induction hypotension and required fewer vasoactive drugs intraoperatively. Regarding the risk of POD, evidence from highly qualified randomized controlled trials is necessary for general anesthesia using remimazolam.

Confirming the study hypothesis would provide an opportunity to reappraise benzodiazepine as a principal anesthetic and broaden the options for intravenous anesthetics currently available. It could offer a rationale for adopting a novel drug anticipating several advantages over propofol. Conversely, rejection of the hypothesis would provide insights into potential side effects clinicians should consider when using the new drug.

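### The exploratory EEG substudy compares patients with and without delirium across both arms and states no treatment term; naming the arm as a stratification factor or covariate is a minor improvement at almost no cost

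*Protocol article*

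**What the plan says.** Section B, under Prespecified additional analyses and substudies, describes the EEG analysis in two sentences. The source is given as "EEG data from the BIS monitoring device will be collected in both groups". The contrast is "The intraoperative EEG profile of patients who do and do not develop POD will be compared". The same sentence adds that the link between the two will be assessed. No model, covariate or stratification factor is named.

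Four other places bear on it:

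- Randomization and blinding: "Patients will be randomly allocated to either the propofol or remimazolam group in a 1:1 ratio".
- Background, on the drug's possible effect on delirium: "It may mitigate POD risk by averting intraoperative hypotension, yet as a benzodiazepine, it could potentially increase the risk".
- Drug class: the Background calls remimazolam a short-acting benzodiazepine, and the Discussion lists propofol among the non-benzodiazepines.
- Anesthetic care sets one depth target for both arms: "The anesthetic depth will be monitored using a BIS monitor (BIS™; Medtronic, Dublin, Ireland) and maintained between 40 and 60".

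The Statistical analysis section has one adjustment rule. It adjusts the treatment effect for covariates on which the two arms turn out to differ.

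**The concern.** The patients are grouped by delirium status, the data come from both arms, and the text names no treatment term. The randomised arm decides which hypnotic is given while the EEG is recorded. By the Background's own account it may also change the risk of delirium. If both links are present, the arm is a common cause of the marker and the outcome. A comparison that ignores it can then show an EEG difference between delirious and non-delirious patients that only reflects which drug they received.

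The general adjustment rule does not repair this. It concerns baseline covariates in the estimate of the treatment effect, so it would not bring the arm into a contrast between patients with and without POD.

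At stake is the reading of an exploratory result. A drug difference could be reported as an EEG marker of delirium. If delirium does not differ by arm, a true marker could be harder to see because the spread between drugs adds to the noise.

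**Working it through.** **Inputs from the article.** Allocation is 1:1. The planned number is 330 per arm before drop-out, so 660 in all. The planning incidence is 31.1% and the margin is 10 points (Sample size). An earlier trial cited in the Discussion found 15.6% with remimazolam and 12.4% with propofol.

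**The plan's own figure.** The substudy states none. The only figure to reproduce is the sample size, which serves here as an input. With unpooled variance and true difference 0, n = (1.96 + 0.8416)² × 2p(1 − p) / 0.10².

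- p = 0.311: 7.849 × 0.4286 / 0.01 = 336.4, so 337.
- p = 0.30: 7.849 × 0.42 / 0.01 = 329.6, so 330.
- Drop-out: 330 / 0.95 = 347.4, so 348 per arm and 696 in all.

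The stated 330 is within about 2% of the value at 31.1%, which is close enough for its use here.

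**Assumption.** Let d be the difference in an EEG feature between the drugs, in within-arm SDs. The article gives no figure, so d is taken as 0.5, 1 and 2. The feature is assumed to have no link to delirium within either arm, so any association found is false.

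**Formulas.** Let f₁ be the share of remimazolam patients among those with POD, and f₀ the share among those without. Ignoring arm:

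- expected false difference = (f₁ − f₀) × d
- variance of the feature in each group = 1 + d² f(1 − f)
- SE = √(variance₁/n₁ + variance₀/n₀)
- z = difference / SE, and rejection rate = Φ(z − 1.96) + Φ(−z − 1.96)

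**Worked case, POD 31.1% vs 41.1% (a difference equal to the whole margin), d = 1.**

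- n₁ = 330 × (0.311 + 0.411) = 238.3 and n₀ = 660 − 238.3 = 421.7.
- f₁ = 0.411 / 0.722 = 0.569 and f₀ = 0.589 / 1.278 = 0.461.
- Difference = 0.108 SD.
- SE = √(1.245/238.3 + 1.248/421.7) = 0.0905.
- z = 1.20, and the rejection rate is 22.4%.

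**All cases, false-positive rate of a nominal 5% test that ignores arm:**

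| POD, propofol vs remimazolam | d = 0.5 | d = 1 | d = 2 |
|---|---|---|---|
| 31.1% vs 31.1% | 5.0% | 5.0% | 5.0% |
| 31.1% vs 34.3% (3.2 points) | 5.5% | 6.8% | 9.5% |
| 12.4% vs 15.6% (cited trial) | 6.0% | 8.3% | 13.4% |
| 31.1% vs 41.1% (full margin) | 9.9% | 22.4% | 47.5% |

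The first, second and fourth rows were checked by simulation with 4,000 runs per cell. Ignoring arm, the rates were 4.6% to 5.1%, then 5.2%, 6.7% and 9.4%, then 10.3%, 21.4% and 48.2%. With an arm term in the model, the rate was 4.4% to 5.3% in every cell.

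**Equal POD.** Here f₁ = f₀ = 0.5, so the false difference is exactly zero for any d. The feature's variance becomes 1 + d²/4, which is 1.0625, 1.25 and 2.0. That is a rise of 6%, 25% and 100%. The standard error rises by the square root, a factor of 1.03 to 1.41.

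**The case against.** The strongest reply is that the text is silent rather than wrong. It never says the arms will be analysed without regard to treatment. It is a two-sentence description in a journal article, and Data management refers to a predefined statistical plan that is not shown, where a treatment term could appear. That stands in part. Analysis regardless of arm is the plain reading of the stated contrast, but it is a reading. What remains is that the contrast itself is fixed in print by delirium status over both arms, and no rule in the article would add the arm.

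Second, a reader might infer that the EEG marker necessarily carries the drug. The article does not say that the EEG differs between remimazolam and propofol. It gives only the drug classes, and both arms share one BIS target. This objection stands in full: d is an assumption, and its range must include modest values such as 0.5. A shared band for one index does not make the rest of the EEG profile equal, but it does not show a difference either.

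Third, a shift in EEG is not enough, since delirium must also differ by arm. This stands too. The large rates need d of about 1 or more together with a POD difference near the full margin.

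Fourth, a reader might go further and say that, because achieved depth is not compared by arm, a delirium result could not be separated from unequal depth. The documents do not support that. Depth arises after randomisation and is part of the effect of each regimen, so it does not bias the randomised comparison. A descriptive table of depth by arm would be ordinary reporting, and the data are already collected.

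**Conclusion.** The point holds as a minor one. Followed as written, the EEG contrast allows confounding by arm, and the article's adjustment rule would not remove it. Under the assumed shift of 0.5 to 2 SDs, the false-positive rate runs from 5% (equal POD), through about 6% to 13% (the cited trial's rates), to about 10% to 47% (a POD difference equal to the margin). Under the equal-incidence assumption that underlies the sample size there is no bias, only the loss of precision shown above.

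It would be too strong to call this a demonstrated error or a threat to the trial. The analysis is an additional substudy and is neither the primary outcome nor one of the twelve listed secondary outcomes. The sample size and the non-inferiority test do not depend on it. The arm is recorded, so nothing in the conduct of the trial is lost.

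**What to change.** Add one sentence to section B. Intraoperative EEG and POD: the association of EEG features with POD will be estimated with treatment arm as a stratification factor or covariate, and a feature-by-treatment interaction will be reported as exploratory. The interaction shows whether the relation differs between the drugs, which a single averaged estimate would hide.

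The cost is one degree of freedom per model for the arm and one more where the interaction is fitted. No new data are needed. The sentence should be settled before the allocation is opened, so that the choice of model cannot follow the result.

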### Data management

Designated investigators will collect perioperative data and record it into a predetermined CRF. An independent investigator then double-enter the data into a password-protected electronic data set. The protected data set will be backed up every 2 months and each patient will be deidentified using a specific identification number in CRF. After the completion of this trial, the data will be reviewed, all data queries will be completed, and the data set will be locked. An independent statistician will access the deidentified data for statistical analyses according to the predefined statistical plan. The principal investigator is responsible for the accuracy and completeness of data. Internal audits will be done by IRB at Samsung Medical Center. The data will be periodically checked for quality, and an independent data monitoring committee (DMC), which consists of two anesthesiologists who are blinded to the group allocation, will meet twice during the study period and monitor the trial process, data management, and patient safety.

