### Safety monitoring

As the administration and dosage of study medications in both anesthesia regimens are within the current clinical practice, we believe that SAEs should be rare. The adverse effects of propofol and remimazolam will be closely monitored during operation by attending anesthesiologists. In case of fetal adverse events, they could stop the infusion of study medications, request the unmaking of group allocation, and inform the principal investigator of any reason for stopping the infusion of study drugs. In addition, a designated investigator will review the occurrence of adverse events possibly caused by study drugs from the start to the end of infusion using chart review. The DMC will perform a review to ensure patient safety. Throughout the study, any adverse events should be reported within 24 h to the DMC.

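### The DMC charged with patient safety is blinded and no by-arm safety review is stated, so no one is assigned to look for an arm imbalance in harms during the trial

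*Protocol article*

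**What the plan says.** The Data management section describes the committee as "two anesthesiologists who are blinded to the group allocation, will meet twice during the study period and monitor the trial process", and the sentence goes on to include data management and patient safety. Safety monitoring repeats the remit: "The DMC will perform a review to ensure patient safety". It also sets the flow of reports: "Throughout the study, any adverse events should be reported within 24 h to the DMC".

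Randomization and blinding fixes when the code may be opened: "Group allocation is only opened when all the collected data are ready for statistical analysis". The next paragraph makes one exception. In a medical emergency, during surgery or afterwards, "the blindness will be unmasked by the request from the attending anesthesiologist to the principal investigator".

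Two other groups are relevant. The treating staff are not blinded: "Anesthesiologists in the operating room cannot be blinded to randomization assignment". They also carry the intraoperative monitoring: "The adverse effects of propofol and remimazolam will be closely monitored during operation by attending anesthesiologists". The protocol further provides for a check of the records, in which "a designated investigator will review the occurrence of adverse events possibly caused by study drugs from the start to the end of infusion using chart" (the quote is cut before its last word). Whether that person is blinded is not stated.

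The independent statistician in Data management appears only after trial completion and data lock. The Statistical analysis section rules out any interim analysis.

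**The concern.** A committee that must protect patients in a two-arm drug comparison has one question that single case reports cannot answer: do harms cluster in one arm? The protocol gives the committee that remit, keeps it blinded, and holds the code back until the end. These are three stated rules that do not fit together. They are not merely a detail left to a longer document.

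At stake are the harms that the protocol itself lists: awareness with recall, undesirable movement (which in its severe grade can mean patient injury), myocardial infarction, cardiac arrest, massive bleeding, and neurologic and non-neurologic complications to 30 days. The test drug is described as newly approved, and 696 patients are to be enrolled. An excess in one arm could run through the whole of enrolment without anyone having the task of looking for it.

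**Working it through.** **Who can see what before the data are ready for analysis**

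| Party | Knows the arm? | Scope | Assigned to compare arms? |
|---|---|---|---|
| DMC | No (Data management) | Individual reports within 24 h; two meetings | No such task stated |
| Attending anesthesiologist | Yes (Randomization and blinding) | Own patients, during the operation | No |
| Designated chart reviewer | Not stated (Safety monitoring) | Events possibly drug-related, start to end of infusion | No |
| Principal investigator, after an emergency request | Yes, for that patient | One patient at a time | No |
| Outcome assessors | No (Randomization and blinding) | Postoperative outcomes | No |
| Independent statistician | Role begins after data lock (Data management) | Final analysis | Not during the trial |

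No row has both knowledge of the arm (real or coded) and the task of comparing arms during enrolment. The arm-aware monitoring that is described ends with the operation. Awareness is asked about at least 6 h after surgery (Adverse events), and complications are collected to 30 days (Secondary outcomes). Both fall outside that window.

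**Illustration of what the labels add**

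The documents give neither harm rates nor the dates of the two meetings. Both are assumed here.

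- Planned total: 696, that is 348 per arm (Sample size). Half enrolment, assumed as a meeting date: 348 in all, 174 per arm.
- Expected events in an arm = 174 × p. Pooled events = 174 × (p1 + p2).

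| Assumed rates | Pooled view | By arm |
|---|---|---|
| 1% v 4% | 174 × 0.05 = 8.7 of 348 (2.5%) | 1.7 v 7.0 |
| 2% v 6% | 174 × 0.08 = 13.9 of 348 (4%) | 3.5 v 10.4 |
| 2% v 8% | 174 × 0.10 = 17.4 of 348 (5%) | 3.5 v 13.9 |
| 5% v 10% | 174 × 0.15 = 26.1 of 348 (7.5%) | 8.7 v 17.4 |

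The pooled total is the same however the events divide between the arms, so it carries no information on imbalance.

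**How much a by-arm table would show**

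Power for a two-sided comparison at 0.05 is Φ[(d − 1.96·se0)/se1], where se0 uses the pooled rate and se1 the separate rates. For 2% versus 6%:

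- se0 = √(0.04 × 0.96 × 2/174) = 0.0210
- se1 = √((0.02 × 0.98 + 0.06 × 0.94)/174) = 0.0209
- power = Φ[(0.04 − 1.96 × 0.0210)/0.0209] ≈ 48%

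The same formula gives about 73% for 2% versus 8% and 42% for 5% versus 10%. With Fisher's exact test the power is lower: about 29% for 1% versus 4% and 37% for 2% versus 6%. Observed splits of 2 versus 7 and 3 versus 10 of 174 give two-sided p = 0.17 and 0.09.

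**The case against.** The strongest reply has four parts.

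1. *Some people do know the arm.* A reader might infer that nobody can see an imbalance and that allocation stays closed without exception until the final analysis. The protocol does not support either reading. Attending anesthesiologists are unblinded and monitor adverse effects, the chart reviewer may see which drug was given, and a single patient can be unmasked in an emergency. This stands, and it limits the point. Intraoperative movement or arrhythmia is visible at once to someone who knows the drug. But these routes work patient by patient, and none is an arm comparison.

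2. *Blinded need not mean pooled.* The article does not say what the DMC is shown at its meetings, and tables under masked A/B labels would be compatible with blinding. A charter or the full protocol may provide for them. It would therefore be wrong to say that the committee is confined to pooled counts. What remains is that the stated rule on opening the code makes no allowance for a safety review by arm, and no one is named to prepare one.

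3. *The risk is said to be small.* Safety monitoring argues that both regimens lie within current practice and that serious adverse events should be rare. That is a fair reason for light monitoring. But when counts are low, their split between the arms is the informative part.

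4. *By-arm tables would often be inconclusive, and the final analyst has no role before lock.* Both statements are correct. Safety review does not rest on a significance threshold, however, and the labels can come from someone other than the final analyst.

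**Conclusion.** The point holds as a gap in assignment: the body responsible for safety is blinded, and no one is given the task of comparing harms by arm during the trial. Emergency unmasking and unblinded anesthesiologists narrow the gap, mainly for intraoperative events, but do not close it for awareness or postoperative complications.

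Its size cannot be taken from the documents. Under the assumed rates and an assumed meeting at half enrolment, a three- to fourfold difference would be invisible in a pooled count of 9 to 17 events. It would be visible, though often not statistically conclusive, in a table by arm. The primary analysis, the sample size of 696 and alpha are untouched. This is an inexpensive improvement and not an error that threatens the trial's conclusion.

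**What to change.** In Data management, state that at each of its two planned meetings the DMC receives tables of deaths, serious adverse events and the perioperative adverse events listed under Secondary outcomes, by masked arm (A/B), with the code available to the DMC on request. Name the independent research assistant who already generates the randomization code as the source of the A/B labels, so that the final analyst need not know which arm is which. State that delirium is left out of these tables. No interim efficacy analysis is then made, the existing statement that none will be performed still holds, and alpha is unchanged.

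In Randomization and blinding, add this exception to the sentence on when allocation is opened, beside the emergency unmasking already described.

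The cost is two sets of tables, two sentences of text, and a coded list that must be kept apart from the investigators. No new members or meetings are needed. The committee stays masked by default, although access to the code on request does qualify its present blinding, and the text should say so.
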